### Sample size calculation

2.2

This study is a multicenter, randomized, double-blind, placebo-controlled trial. The primary outcome is a continuous variable. The allocation ratio between the SXYX group and the placebo group is 1:1. The sample size will be calculated using the formula for comparing two independent means. The formula is as follows:$$n_{1}=n_{2}=2{\left[\frac{(Z_{\alpha /2}+Z_{\beta })\sigma }{\delta }\right]}^{2}$$Based on preliminary data from a small-sample, exploratory pilot study, the peak oxygen consumption (VO_2_ peak) in patients with HFpEF after 6 months of treatment was 20.2 ± 4.8 mL/kg/min in those receiving Chinese herbal medicine, and 18.9 ± 4.2 mL/kg/min in those receiving standard conventional medical therapy. The standard deviations of 4.8 and 4.2 from the preliminary data were used solely to estimate the population standard deviation (*σ*). Based on the OptimEx-Clin Study (21), the latest prognostic studies of percentage of predicted peak VO_2_ in HFpEF (22), and the published results of traditional Chinese medicine for HFpEF with the Qi-deficiency and blood-stasis pattern (23), the minimal clinically important difference for sample size calculation was set at 2.7 mL/kg/min.$$\sigma^{2}=(S_{{}_{1}}^{2}+S_{2}^{2})/2=(4.8^{2}+4.2^{2})/2=20.34$$$$n_{1}=n_{2}=2{\left[\frac{(Z_{\alpha }+Z_{\beta })\sigma }{\delta }\right]}^{2}=2\left[\frac{{\left(1.96+1.282\right)}^{2}\times 20.34}{2.7^{2}}\right]\approx 59$$The calculation yielded approximately 59 patients per group. Accounting for an anticipated 20% dropout rate, the required sample size was adjusted to 74 patients per group, resulting in a total enrollment of 148 patients.

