#### Primary outcome

2.14.1

Change from baseline to 24 weeks in peak VO_2_ as assessed by CPET.

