### Statistical analysis

2.18

Statistical analyses will be performed using SPSS Statistics 32.0 (IBM Corp., Armonk, NY, USA) and R 4.2 (for mixed models). Three analysis populations are defined: (i) the modified intention-to-treat (mITT) set, comprising all randomized patients who received at least one dose of the study drug and had at least one post-baseline primary efficacy assessment—this serves as the primary analysis set; (ii) the per-protocol set (PPS), including patients who completed the 24-week trial without major protocol deviations, used for sensitivity analyses; and (iii) the safety set (SS), including all patients who received at least one dose of the study drug, used for safety analyses. Baseline and descriptive analyses: Baseline demographic and clinical characteristics (including age, sex, BMI, aetiology of heart failure, LVEF, NT-proBNP, SGLT2i use rate, etc.) will be compared between the two groups using independent-samples *t*-tests for continuous variables with normal distribution, Mann–Whitney *U* tests for continuous variables with non-normal distribution, or chi-square tests for categorical variables, in order to describe the balance after randomization. For safety analyses, comparisons of the incidence of adverse events between groups will also be performed using chi-square tests or Fisher's exact test. Primary endpoint analysis: The change in peak VO_2_ from baseline to week 24 is designated as the sole primary efficacy endpoint (week 12 change is reclassified as a key secondary endpoint). The primary analysis will be performed using a mixed-effects model for repeated measures (MMRM) rather than ANCOVA, with fixed effects including treatment group, visit (baseline, week 12, week 24), treatment-by-visit interaction, baseline peak VO_2_, baseline SGLT2 inhibitor use (yes/no), and study center. The MMRM was chosen because it uses all available longitudinal data and accounts for the correlation between repeated measurements within each subject, whereas ANCOVA would be limited to a single post-baseline time point and would not adequately handle the repeated-measure structure. Subject is included as a random effect (random intercept). The treatment effect will be reported as adjusted least-squares mean difference with 95% confidence intervals. Secondary endpoint analysis: Key secondary endpoints (including change in peak VO_2_ at week 12, NT-proBNP, 6-minute walk test, and NYHA functional class) will be analyzed using the same MMRM for continuous variables or logistic regression for categorical variables (with NYHA class dichotomized as improvement ≥1 grade vs. no improvement). To control type I error inflation due to multiplicity, a fixed-sequence testing procedure is prespecified: formal hypothesis testing for these four key secondary endpoints will proceed only if the primary endpoint (week 24 peak VO_2_) is statistically significant (*P* < 0.05), in the following order: ① week 12 peak VO_2_ change → ② NT-proBNP → ③ 6MWT → ④ NYHA class improvement (≥1 grade). All other secondary endpoints (including echocardiographic parameters, TCM syndrome score, individual symptoms/signs, EQ-5D, and coagulation function) are designated as exploratory/supportive endpoints, for which only descriptive statistics and unadjusted *P*-values will be reported; between-group comparisons for these exploratory endpoints will be performed using *t*-tests or Mann–Whitney *U* tests as appropriate, with unadjusted *P*-values provided for descriptive reference only, explicitly labelled as hypothesis-generating and not subject to formal inferential conclusions; hence, no multiplicity adjustment is applied to them. Center heterogeneity: Study center is included as a fixed effect in all MMRM models to account for potential variations in CPET execution, background care, and baseline characteristics across sites, ensuring robustness of the pooled treatment estimate.

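### The primary mixed model uses baseline peak VO2 both as a response visit and as a covariate under a random intercept, so the week-24 adjusted mean difference is tested above its nominal 5% level

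*Protocol article*

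**What the plan says.** Section 2.14.1 defines the primary outcome as "Change from baseline to 24 weeks in peak VO_2_ as assessed by CPET", and section 2.18 repeats that "The change in peak VO_2_ from baseline to week 24 is designated as the sole primary efficacy endpoint".

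For the primary model, section 2.18 gives treatment group as a fixed effect together with "visit (baseline, week 12, week 24), treatment-by-visit interaction, baseline peak VO_2", and adds SGLT2 inhibitor use at baseline and centre. The within-patient structure is "Subject is included as a random effect (random intercept"). The result is described only as follows: "The treatment effect will be reported as adjusted least-squares mean difference with 95% confidence intervals". The contrast is not named further.

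The four key secondary endpoints are tested in fixed order only if "the primary endpoint (week 24 peak VO_2_) is statistically significant (*P* < 0.05"). The continuous ones use the same model; NYHA class improvement uses logistic regression.

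Section 2.11.3.1 adds time-varying covariates for major medication adjustments and cumulative diuretic exposure. Nothing in the article removes the baseline rows from the response or gives another covariance structure.

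**The concern.** Baseline can enter a repeated-measures model as a covariate, with post-baseline visits as the response. Or it can enter as a response visit, with no baseline covariate. The article does both at once.

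On the change scale every baseline row is exactly zero. On the raw scale the baseline row is largely explained by its own covariate. The two scales give the same model: replacing Y by Y − B only shifts the coefficient of B by 1.

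A random intercept implies one residual variance and one correlation for all three visits. The nearly noise-free baseline rows therefore lower the variance estimate that is then applied at week 24. At stake are the p-value and confidence interval of the only primary test, and the gate to the key secondary tests.

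**Working it through.** **Inputs from the article (section 2.2).** SDs 4.8 and 4.2, of which the article says "The standard deviations of 4.8 and 4.2 from the preliminary data were used solely to estimate the population standard deviation"; difference 2.7 mL/kg/min; Z values 1.96 and 1.282; 20% dropout. The test level of 0.05 is in section 2.18.

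**The plan's own figure reproduces.** σ² = (4.8² + 4.2²)/2 = 20.34, so σ = 4.51. n = 2 × (1.96 + 1.282)² × 20.34 / 2.7² = 58.65, rounded up to 59 per arm. 59/0.8 = 73.75, so 74 per arm and 148 in total. The sample-size arithmetic is not at issue.

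**Rough analytic check.** Let two visits have residual variance v and one have 0. A common variance is then 2v/3, and the ratio of stated to true standard error is √(2/3) = 0.82. The actual two-sided error is 2[1 − Φ(1.96 × 0.816)] = 2[1 − Φ(1.60)] ≈ 11%.

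**Simulation under no treatment effect.** Rows for baseline, week 12 and week 24; fixed effects treatment, visit, treatment-by-visit, baseline peak VO2, SGLT2 inhibitor use and centre; random intercept fitted by REML; SD 4.5; 59 or 74 per arm; 3,000 to 10,000 trials per setting. *Assumption:* the visit correlations are not in the article. They were set equal (0.3 to 0.9) or falling with time (correlation of weeks 12/24 with baseline from 0.7/0.5 to 0.9/0.8).

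Rejection at nominal 5%:

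| Setting (n per arm) | Week-24 LS-mean difference | Week 24 minus baseline interaction | Post-baseline rows only, random intercept | Week-24 ANCOVA |
|---|---|---|---|---|
| Equal 0.3 (59) | 9.0% | 5.1% | 4.7% | 4.8% |
| Equal 0.7 (59) | 9.7% | 4.8% | 4.7% | 4.8% |
| Equal 0.9 (74) | 9.9% | 4.6% | 4.7% | not run |
| Falling 0.85/0.8 (59) | 12.4% | 7.0% | 6.6% | 5.1% |
| Falling 0.8/0.7 (59) | 13.9% | 8.9% | 7.4% | 5.4% |
| Falling 0.7/0.5 (74) | 14.5% | 9.7% | 7.6% | not run |
| Falling 0.9/0.8 (74) | 16.1% | 11.0% | 8.1% | not run |
| Equal 0.7, 20% missing at week 24 (74) | 9.7% | 5.1% | 4.5% | not run |
| Falling 0.8/0.7, 20% missing at week 24 (74) | 14.8% | 9.1% | 7.3% | not run |

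Over all settings run:
- Week-24 LS-mean difference: 9.0–10.4% under equal correlation, 12.4–16.2% under falling correlation.
- Interaction contrast: 4.6–5.2% and 7.0–11.0%.
- Post-baseline rows only, random intercept: 4.5–5.5% and 6.4–8.8%.
- Week-24 ANCOVA, close to a post-baseline model with unstructured covariance on complete data: 4.8–5.5% where run.

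**The standard errors explain the rates.**
- Equal 0.7: mean model SE 0.502 against a true SD of the estimate of 0.597, ratio 0.841. 2[1 − Φ(1.96 × 0.841)] ≈ 9.9%; simulated 9.7%.
- Falling 0.8/0.7: 0.462 against 0.609, ratio 0.759. 2[1 − Φ(1.96 × 0.759)] ≈ 13.7%; simulated 13.9%.

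Across settings the model SE is about 13–28% too small.

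**Averaged over visits.** A difference averaged over all three visits rejects about 5% of the time (4.9–5.9%). It includes a visit with no true effect, so a constant 2.7 would be reported as (0 + 2.7 + 2.7)/3 = 1.8.

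**The case against.** The strongest reply is that the inflation belongs to one contrast. The endpoint is change from baseline to week 24, and with baseline as a visit level the treatment-by-visit term estimates that change directly. Under equal correlation this contrast keeps 5%. That stands, and it rules out an unconditional statement that the primary test runs at 9–14%, which a reader might infer. It does not clear the plan. The article reports an adjusted least-squares mean difference for a week-24 endpoint, whose natural reading is the week-24 difference. The interaction contrast is also inflated once correlation falls with time.

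Other limits also stand:

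- **Cause.** Under falling correlation part of the excess comes from the random intercept itself: the model without baseline rows still runs at about 6–9%. The double use of baseline is not the whole explanation.
- **Dilution.** A reader might infer that the trial would both over-reject and report 1.8 for 2.7. These belong to different contrasts, and the averaged one keeps about 5%. Averaging is also the weaker reading, since section 2.18 names week 24 as primary and makes week 12 a separate key secondary.
- **Key secondaries.** A reader might infer that all four share the faulty model. NYHA class does not.
- **Scope of the simulation.** The time-varying covariates of section 2.11.3.1 were not included. Nothing suggests that they would remove the problem, but their effect was not tested.

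It could also be said that a condensed article leaves model detail to the analysis plan. Here, however, the article itself fixes the visit levels, the covariate and the covariance structure, and the combination is wrong.

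**Conclusion.** The primary model is wrongly specified as written. For the natural reading of the stated estimate, the week-24 adjusted mean difference, true type I error is about 9–16% at nominal 5%. It was at least 9% in every correlation setting tried. For the interaction contrast it is about 5% under equal correlation and about 7–11% under falling correlation. These rates rest on assumed visit correlations and are not bounds.

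Under the week-24 reading the primary 95% confidence interval is too narrow. The fixed-sequence procedure then does not hold its 5% level, because its gate does not; the continuous key secondaries inherit the same model. The documents do not support a single error rate for the trial, or the claim that every key secondary is affected.

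**What to change.** Rewrite the primary model in section 2.18:

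1. Use weeks 12 and 24 only as response visits and keep baseline peak VO2 as a covariate. Alternatively, keep baseline as a response visit with equal arm means imposed and drop the baseline covariate.
2. Replace the random intercept by an unstructured within-patient covariance. Removing the baseline rows alone leaves about 6–9% under falling correlation.
3. Name the week-24 treatment contrast as the primary estimate.
4. Apply the same form to the continuous key secondaries.

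A baseline-by-visit term and Kenward–Roger degrees of freedom are optional refinements. The cost is protocol and analysis-plan wording, to be settled before unblinding; the visit schedule and enrolment figures need not change for this point. The one downside is a wider confidence interval than the current model would print, and that wider interval is the correct one.

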
## Discussion

3

Globally, the incidence, prevalence, hospitalization rate, and non-cardiovascular mortality of HFpEF are all higher than those of HFrEF, making it the predominant form of heart failure in the globally aging population and imposing a substantial disease and economic burden on society (31–33). Although modern medicine has made notable progress in the treatment of HFpEF, the underlying mechanisms remain incompletely understood. To date, only caloric restriction, exercise training, SGLT2 inhibitors, and dual SGLT1/2 inhibitors have demonstrated clinical benefit (31). HFpEF is a highly complex clinical syndrome often associated with multiple comorbidities such as diabetes, hypertension, and atrial fibrillation. More than 95% of patients with HFpEF have two or more such comorbidities (6). Therefore, single-target pharmacological therapy in modern medicine often fails to achieve optimal outcomes, leaving the clinical needs of HFpEF patients unmet. TCM emphasizes treatment based on syndrome differentiation. The theory of “treating different diseases with the same method” (Yì Bìng Tóng Zhì), which means that different diseases can be treated with the same herbal formula based on the same underlying syndrome, is a unique strength of TCM and is particularly well-suited for managing complex clinical syndromes such as HFpEF.

The composition of SXYX follows a rigorous principle of herb compatibility. The sovereign herbs, raw *Hedysarum Multijugum Maxim*, *Codonopsis Radix*, and *Cimicifugae Rhizoma*, supplement Qi and elevate sunken Qi, and carry the effects of the formula upward. The minister herbs, *Radix Paeoniae Rubra*, *Curcumae Rhizoma*, *Trichosanthes Kirilowii Maxim*, *Allium Azureum Ledeb*, *Arum Ternatum Thunb*, and *Radix Bupleuri*, activate blood circulation and resolve stasis, as well as eliminate phlegm and remove turbidity. The assistant herbs, *Cinnamomi Ramulus* and *Lepidii Semen Descurainiae Semen*, unblock Yang, transform Qi, and promote diuresis; *Anemarrhenae Rhizoma* clears heat and nourishes Yin, counterbalancing the warm-dry nature of the Qi-supplementing herbs. The messenger herb, *licorice*, harmonizes the actions of the various ingredients and protects the middle burner (spleen and stomach). The overall effect of the formula is to supplement Qi and activate blood circulation, making it particularly suitable for treating HFpEF with the syndrome of Qi deficiency and blood stasis. HFpEF is secondary to comorbidity-driven systemic inflammation, progressive fibrosis, and myocardial cell injury (31). Preclinical evidence has suggested that flavonoids derived from *Astragalus membranaceus* inhibit Th1 and Th17 cell differentiation and increase regulatory T cell (Treg) levels, thereby reducing inflammatory damage (34). It has also been shown in animal studies that astragaloside IV and *Astragalus* polysaccharide (APS) regulate the aberrant activation of the TGF-β1/Smads pathway, downregulate p38 MAPK and NF-κB/p65 phosphorylation levels, and inhibit myocardial fibrosis (35). Additionally, studies based on isolated compounds have indicated that total paeony glycoside (TPG) inhibits the activation of the NLRP3 inflammasome and alleviates the inflammatory response (36). Similarly, experimental evidence suggests that the β-sitosterol component of Gualou Xiebai Banxia Decoction reduces the levels of IL-1β, IL-6, and TNF-α in endothelial cells, thereby inhibiting inflammatory responses, cardiomyocyte apoptosis, and myocardial fibrosis (37, 38). Preclinical data have also demonstrated that cinnamaldehyde exerts anti-inflammatory effects by modulating multiple signaling pathways, including TLR4, TRAF6, NF-κB, JAK/STAT, and Nrf2, through the regulation of inflammatory cytokines such as TNF-α, IL-1β, and IFN-γ (39). Furthermore, findings from rodent models suggest that the aqueous extract of *Lepidii Semen Descurainiae Semen* (Tinglizi) activates the PI3K/Akt/mTOR signaling pathway, inhibits apoptosis, and ameliorates ventricular remodeling in rats with heart failure (40). Finally, one preclinical study has shown that Shengxian Yixin Granule inhibits myocardial fibrosis, delays ventricular remodeling, and improves cardiac function in rats with myocardial infarction via the PI3K/AKT signaling pathway (41). Taken together, it may be hypothesized that SXYX could exert its therapeutic effects on HFpEF through multiple pathways, including the inhibition of inflammatory responses, myocardial fibrosis, and apoptosis. However, it is important to note that the above mechanistic evidence is primarily derived from individual herbs, isolated compounds, or animal models; these findings should be interpreted as providing biological plausibility rather than proof of the mechanism of action of the complete SXYX formula in patients with HFpEF. Confirmation of these mechanistic hypotheses in the current human trial is warranted.

Patients with HFpEF typically present with dyspnea and reduced exercise tolerance as their classic clinical features. CPET assesses dyspnea and gas exchange during exercise, and serves as an important tool for assisting in the diagnosis and risk stratification of HFpEF (42). CPET is a safe, non-invasive, incremental-load exercise test. During CPET, peak VO_2_ refers to the highest oxygen consumption achieved during maximal exercise. This parameter reflects the metabolic status of HFpEF patients and is also an important prognostic indicator in patients with chronic heart failure (CHF) (43). In the early stages of the disease, NT-proBNP levels and their dynamic changes are of great prognostic value in predicting long-term outcomes in patients with HFpEF (44). Myocardial fibrosis is one of the key pathological features of HFpEF. NT-proBNP levels are associated with markers of myocardial fibrosis in HFpEF and are associated with an increased risk of adverse events (45). Therefore, using CPET-derived parameters and NT-proBNP as efficacy measures to evaluate the therapeutic effects and clinical prognosis of SXYX in patients with HFpEF is of significant clinical value.

The major innovation of this study lies in the following aspect: Given that traditional cardiopulmonary exercise testing can only be performed in a hospital setting and cannot reflect patients’ daily exercise tolerance, this study overcomes the limitations of the traditional single-modality assessment of exercise tolerance in HFpEF patients by introducing wearable monitoring devices to achieve out-of-hospital, real-time, long-term, and dynamic capture of patients’ cardiopulmonary exercise data, including heart rate, blood oxygen saturation (SpO_2_), step count, walking distance, and other parameters, thereby establishing a comprehensive evaluation model consisting of in-hospital standardized assessment plus out-of-hospital long-term dynamic monitoring. This model will evaluate the clinical efficacy of SXYX in treating HFpEF from multiple dimensions. Meanwhile, the protocol has been designed in strict accordance with the SPIRIT 2025 guidelines to ensure the generation of high quality clinical evidence. In summary, this study will provide an objective, pragmatic, and patient centred evaluation of the therapeutic efficacy of SXYX in a real world setting, thereby offering high level evidence to support their clinical application. Future research should focus on exploring the integration of wearable-derived digital biomarkers into routine clinical decision-making for HFpEF.

## Ethics statement

This study was approved by the Ethics Committee of The First Affiliated Hospital of Henan University of Chinese Medicine on 14 February 2026 (approval No. 2026HL-041-01) and was registered with the ITMCTR under registration number ITMCTR2026000833. The participants provided their written informed consent to participate in this study.
